##### Inclusion criteria

 Current registration with a provincial licensing boards and in active private practice in Canada; Graduation at least 1 year ago; Provision of chiropractic treatment to a minimum of two adults (age 18–65) with neck pain per week; Fluent in spoken English or French; and Access to the internet.

##### Exclusion criteria

Chiropractors will be excluded if they have already attended the webinar series or the self-management learning module. To date, over 700 Canadian chiropractors have registered for both the webinars and the self-management learning module, of whom over 475 have either completed it or are in progress of doing so. Prior registration provides the mechanism for confirming study ineligibility.

#### Recruitment of patients

Participating chiropractors will each recruit up to five consecutive new patients with neck pain. A recruitment/advertisement notice will be posted in each participating chiropractor’s waiting room. The expected recruitment of 5 patients within 3 months is reasonable assuming an average practice volume of 85 patient visits per week per chiropractor, of whom 25 % are expected to have neck pain [6].

##### Inclusion criteria

 Aged between 18 and 65 years, with a primary complaint of acute (<3 months) or chronic (>3 months) neck pain presenting as a new condition for treatment at the participating clinic; A diagnosis of NSNP (of any duration); Able to understand and speak English to complete all study questionnaires (which will be assessed by a designated member of the chiropractor’s office personnel at the time of screening).

##### Exclusion criteria

 Previous neck surgery;Presence of “red flags” (alerting the possibility of serious conditions such as malignancy, infection, fracture, inflammatory arthropathies including rheumatoid arthritis or vascular disease of the neck); Pregnancy; and Chiropractic care received in the preceding 3 months for a complaint of neck pain.

### Measures

The key feasibility outcomes of interest include (1) study recruitment/participation, (2) adherence to the intervention, (3) study retention, and (4) KT intervention effectiveness potential. Table 1 provides the different criteria for defining the outcomes derived from items (1) to (4) above. Table 2 further summarizes the feasibility outcomes, sources of measurement, and timing of administration.

**Table 1 Tab1:** Criteria to assess feasibility

Construct	Parameter
	Eligibility proportion
Chiropractors	
Recruitment	Trial acceptance rate: >20 % agree to participate within 4 weeks
	Target population = 40 (assuming an 80 % retention rate)
Adherence to protocol	>90 % of participants will complete all 3 webinars, associated quizzes, 2 clinical vignettes, and a self-management learning module
Retention	80 % of participants will complete 3 months of patient follow-up
Patients	
Recruitment	Trial acceptance rate: 5 patients within 6 weeks of recruitment notice
	Target population = 150
Adherence to protocol	95 % will attend regular treatment sessions twice/week
	>80 % will comply with prescribed home exercise and physical activity
Retention	>80 % will complete patient encounter forms (VAS, NDI, and PSQ-18) and follow-up at 3 months

**Table 2 Tab2:** Outcome measures

Outcome	Source	Description of measures	Data collection time points	
Feasibility				
Recruitment	Chiropractors and patients	Measured as a proportion of chiropractors and patients potentially eligible for participating	Initial stage	
		Eligibility rate = number of eligible chiropractors and patients divided by the number of invited chiropractors or patients		
		Participation rate = number of chiropractors and patients agreeing to participate divided by number of eligible chiropractors and patients		
Adherence to protocol	Chiropractors	For those randomized to intervention arm, measured through the rates of attendance of all 3 webinars, associated quizzes, completion of 2 clinical vignettes, and the self-management learning module	Within 6 weeks of assignment	
	Patients	Rate of adherence to follow-up visits, prescribed home exercise, and physical activity	Baseline	3 months
Adherence perception (knowledge and self-efficacy)	Chiropractors and patients	Completion of questionnaires	Baseline	3 months
Retention	Chiropractors and patients	Retention rate = number of chiropractors or patients who completed follow-up of all outcome measures at 3 months divided by number of chiropractors or patients who were randomized	Baseline	3 months
	Chiropractors	Rate of completion of patient encounter forms and questionnaires including levels of knowledge and self-efficacy and the BAP	Baseline	3 months
	Patients	Rate of completion of patient encounter forms and questionnaires including the BAP, visual analogue scale (VAS), Neck Disability Index (NDI), and satisfaction with care	Baseline	3 months

Differential retention and adherence rates across the randomized groups will also be measured

Expected adherence to multimodal care by chiropractors will be measured at the end of the study using a short self-administered questionnaire that will include items about knowledge (e.g. “I am following the recommendations regarding the use of clinical practice guidelines and multimodal approach for neck pain”) and self-efficacy (e.g. (i) “I am confident that I will not encounter difficulties in delivering multimodal care” and (ii) “If I encounter difficulties, I am confident that I can still offer multimodal care”) [29, 35, 36]. End-of-study questionnaires will also include the Brief Action Planning (BAP) skill survey and clinician experience in using the BAP tool in practice (Additional file 1).

Expected adherence to multimodal care by patients will also be assessed at baseline using a specific questionnaire item (e.g. “I intend to perform the neck exercises that were prescribed for my condition”). Furthermore, compliance with guideline recommendations at the patient level will be measured using a checklist documenting the extent of their confidence in managing most of their health problems, the type of help received from their treating chiropractor, and the use of exercise and self-care prescriptions, as well as their levels of compliance with recommended exercises (Additional file 1). Furthermore, patient-related health outcomes will be collected at baseline and at 3 months through the use of questionnaires to measure symptoms, impairment, activity interference at home and at work, general quality of life, and satisfaction with care (PSQ-18). The minimal clinically important difference (MCID) in the 10-cm VAS pain score will be measured as the mean difference between current and baseline scores among patient participants who report feeling either “a little worse” or “a little better” in terms of their global self-perceived change. Otherwise, a 10 % change from baseline will be considered minimal change, while a 30 % change from baseline will be considered a substantial and clinically important change [37].

The Neck Disability Index (NDI) is a 10-item self-administered questionnaire, scored from 0 to 50 with a higher score representing more disability. A score of 0 to 4 represents no disability, a score >35 represents complete disability, and a score >25 represents severe disability. An absolute change of 10 points or relative change of 20 % on the NDI will be considered clinically important [38].

Feasibility to conduct a larger study will also be determined by estimating the effect size (and subsequently, the anticipated sample size) needed for a future main trial. Challenges encountered by participating clinicians while conducting the trial will be assessed by administering an end-of-study questionnaire and conducting interviews. An open-ended question will be used to elicit the chiropractors’ experiences (challenges or facilitators) encountered while trying to comply with the guideline recommendations.

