**Methods/design:**

The design is a cluster-randomized controlled pilot and feasibility trial. Chiropractors in private practice in Canada will be approached to participate in the study. Thirty consenting chiropractors will be randomized to receive either a theory-based educational intervention in the experimental group or simply a printed copy of the guideline in the control group. Each chiropractor will recruit five neck pain patients (a total of 150 patients) into the study. Development of the multifaceted intervention was informed by the results of a related qualitative study based on the Theoretical Domains Framework and consists of a series of three webinars, two online case scenarios, a self-management video on Brief Action Planning, and a printed copy of the practice guideline. *Primary feasibility outcomes* for both chiropractors and patients include rates of (1) recruitment, (2) retention, and (3) adherence to the intervention. A checklist of proxy measures embedded within patient encounter forms will be used to assess chiropractors’ compliance with guideline recommendations (e.g. exercise and self-care prescriptions) at study onset and at 3 months. Secondary outcomes include scores of behavioural constructs (level of knowledge and self-efficacy) for recommended multimodal care. *Clinical outcomes* include pain intensity and neck pain-specific disability. Analyses from this study will focus on generating point estimates and corresponding 95 % confidence intervals for parameters of a priori interest (recruitment, retention, adherence, pain intensity, Neck Disability Index).

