### Research question and objectives

The research question of interest for a larger main study is the following: Among chiropractors in Canada, to what extent does the effectiveness of a multifaceted theory-based complex educational KT intervention plus provision of a copy of the CPG (for the intervention group) enhance behavioural change and compliance with a multimodal care programme when compared to the distribution of CPGs alone (for the control group) for the management of NSNP-related pain and disability over 3 months?

The immediate primary objective of the current pilot study is to provide evidence for the feasibility of conducting a fully powered cluster RCT to evaluate a complex KT intervention. Feasibility will be evaluated in terms of rates of recruitment, retention, and adherence to the study protocol. We will ascertain how closely participating chiropractors and patients adhere to the study protocol and will solicit feedback from them about the overall usefulness of the content and format of the KT intervention. The potential effectiveness of the complex KT intervention will also be estimated. Again, the results of this pilot trial will be used to design a full-scale cluster-randomized trial.

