### Specific objectives

The specific objectives target two groups of participants: chiropractors and patients. For each group, both feasibility and efficacy potential will be estimated.For chiropractors, the feasibility objectives are to estimate the proportion who Are eligible to participate and are willing to be randomized; Comply to all study procedures, including completing the KT intervention component and implementing the CPG recommendations; and Complete the 3-month follow-up evaluation.
For patients, the feasibility objectives are to estimate the proportion who Are eligible to participate and are willing to be randomized; Adhere to all study procedures; and Complete the 3-month follow-up visit and all questionnaires.
For chiropractors, the efficacy potential objectives are to estimate The extent to which knowledge and self-efficacy changes after engaging in the KT intervention and CPG and The extent to which knowledge and self-efficacy changes after engaging in CPG.
For patients, the efficacy potential objective is To estimate the effect of their chiropractor’s KT intervention and CPG implementation changes in pain, disability, and satisfaction with care at the initial phase, as well as after 3 months of follow-up.
Other secondary objectives are to identify and provide solutions to Chiropractors’ concerns about the quality of the webinars; Potential impediments to successful initiation of the main study protocol after randomization; and Challenges that participating clinicians have with managing the study (e.g. with implementing the multimodal care and/or completing initial and follow-up questionnaires).

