For the efficacy potential analysis, we will estimate the proportion of chiropractors who endorsed a higher knowledge level post-intervention in the control group and use this as the basis for calculating the probability of achieving a response more extreme than this in the intervention group using the normal approximation to the binomial distribution (stattrek.com). For example, if 2 of 15 participants in the control group endorse a higher knowledge level, this yields an expected “success” proportion of 0.13. Based on this expected proportion or probability, if 5 or more of the 16 chiropractors in the intervention group endorsed a higher knowledge response, the probability of this occurring by chance would be 0.047. This approach will be used for each of the single indicator variables under study here (i.e. knowledge and self-efficacy).

We will use generalized estimating equations (GEEs) to adjust for anticipated correlation in measurements of observations within practices (clusters). For pain and disability, GEE will be used separately for each of these outcomes and to examine for any effect of our complex intervention over time (the follow-up period). This method extends the standard regression analysis to account for any covariance between repeated measurements of pain and disability (as separate outcomes) over time, in addition to accounting for anticipated correlation of observations within practices.

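### Effectiveness potential is listed as a fourth key feasibility outcome with no criterion, although the abstract and objectives define feasibility by three rates alone

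*Protocol article*

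**What the plan says.** The Protocol article describes the feasibility outcomes in several places.

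- **Abstract, Methods/design.** The primary feasibility outcomes "for both chiropractors and patients include rates of (1) recruitment, (2) retention, and (3) adherence to the intervention". Knowledge and self-efficacy scores are secondary outcomes; pain and disability are clinical outcomes.
- **Research question and objectives.** "Feasibility will be evaluated in terms of rates of recruitment, retention, and adherence to the study protocol". Effectiveness is an addition: "The potential effectiveness of the complex KT intervention will also be estimated".
- **Specific objectives.** "For each group, both feasibility and efficacy potential will be estimated", with separate lists of objectives for each.
- **Measures, opening paragraph.** The key feasibility outcomes are the three rates and a fourth: "3) study retention, and (4) KT intervention effectiveness potential". The next sentence reads "Table 1 provides the different criteria for defining the outcomes derived from items (1) to (4) above".
- **Measures, last paragraph.** "Feasibility to conduct a larger study will also be determined by estimating the effect size". The sentence goes on to mention the sample size for a future main trial.
- **Statistical analysis.** The control-group proportion with improved knowledge is taken as the expected proportion, and a chance probability is computed for the intervention-group count. The worked example gives 0.047. Then: "This approach will be used for each of the single indicator variables under study here", meaning knowledge and self-efficacy. Pain and disability each get their own GEE model.

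**The concern.** Whether a full cluster trial is feasible is the main question this pilot is meant to answer. The document gives two lists of what answers it. Under the abstract and objectives, three rates do. Under Measures, effectiveness potential has equal standing with them, and the reader is sent to Table 1 for a criterion that is not there.

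If the fourth item counts, nothing says what result on it would support or undermine feasibility, or on which measure. An effect estimate from a few dozen chiropractors could then be brought into the feasibility conclusion, or left out of it, after the data are seen. The one numerical device offered for effectiveness potential, the chance probability in Statistical analysis, is also a weak basis for that use.

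**Working it through.** **1. The lists side by side**

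| Place | Recruitment | Retention | Adherence | Effectiveness potential |
|---|---|---|---|---|
| Abstract | primary feasibility | primary feasibility | primary feasibility | not in the list; knowledge and self-efficacy secondary |
| Research question and objectives | feasibility | feasibility | feasibility | estimated in addition |
| Specific objectives | feasibility | feasibility | feasibility | separate objectives |
| Measures, opening | key feasibility | key feasibility | key feasibility | **key feasibility, item (4)** |
| Table 1 | criterion given | criterion given | criterion given | **none** |
| Table 2, feasibility block | row | row | row | no row |

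Table 1 also carries an eligibility heading, but nothing on effect. Take a pilot that meets every Table 1 target. By the objectives it is feasible. By the opening of Measures one of its four key outcomes cannot be judged, so its status is undetermined.

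**2. The plan's worked figure**

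Inputs from Statistical analysis: control 2/15, rounded to 0.13; intervention 5 or more of 16; stated probability 0.047.

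- Exact binomial, P(X ≥ 5 | n = 16, p = 0.13) = 0.0471. This reproduces 0.047.
- The same with p = 2/15 unrounded: 0.0517.
- Normal approximation, the method the text names, with p = 0.13: mean 16 × 0.13 = 2.08, SD √(16 × 0.13 × 0.87) = 1.345. Without continuity correction, z = (5 − 2.08)/1.345 = 2.17, P = 0.015. With it, z = (4.5 − 2.08)/1.345 = 1.80, P = 0.036.
- Fisher's exact test, which treats both groups as samples, 5/16 against 2/15: one-sided 0.22, two-sided 0.39.

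The printed figure is thus an exact binomial tail at the rounded proportion. It falls below 0.05 largely because the control proportion is treated as known.

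**3. Null error of that rule**

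Assumptions: 15 control and 16 intervention chiropractors, as in the example; the same true response rate in both arms; exact tail; a result called positive when the probability is below 0.05. The 0.05 is assumed; the document states no alpha. With c control responders, the rule uses p = c/15 as if known. The error is the sum over c and x of P(c | 15, p) × P(x | 16, p) for all pairs that the rule calls positive.

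| True rate in both arms | Null error | Part from c = 0 |
|---|---|---|
| 0.10 | 0.192 | 0.168 |
| 2/15 | 0.151 | 0.105 |
| 0.20 | 0.114 | 0.034 |
| 0.30 | 0.111 | 0.005 |
| 0.40 | 0.117 | <0.001 |
| 0.50 | 0.102 | <0.001 |

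The last column is (1 − p)^15 × [1 − (1 − p)^16]: with no control responders, the rule gives probability zero to any intervention response. At p = 0.10 this is 0.206 × 0.815 = 0.168. So at low response rates most of the excess comes from an empty control cell. From 0.30 upwards it comes from ignoring the sampling error of the control proportion. Over the range the error is 0.10 to 0.19 per indicator, two to four times the assumed 5%.

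**4. The same example as an estimate**

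Difference 0.3125 − 0.1333 = 0.179. SE = √(0.3125 × 0.6875/16 + 0.1333 × 0.8667/15) = 0.145. Simple 95% interval: 0.179 ± 1.96 × 0.145 = −0.11 to 0.46. This shows how little the example says about direction or size.

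**The case against.** The strongest reply is that the intent is clear and only a list and a cross-reference are wrong. The abstract ranks the outcomes. The objectives separate feasibility from efficacy potential. Statistical analysis opens with descriptive feasibility statistics and gives effect size a planning role, in choosing a primary outcome and sizing the full-scale study. The effect-size sentence in Measures, read to its end, also concerns the sample size of the main trial. This stands as evidence of intent, and it is why the repair is small. It does not remove the conflict: item (4) is expressly called a key feasibility outcome, and the criterion promised for it is absent. An article may leave detail to the full protocol, but here the text says the criterion is in a table that it prints.

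A reader might infer more than the document supports:

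- **That a null effect would make the trial infeasible, or one positive indicator would make it feasible.** No such rule is stated, nor any formal go/no-go rule. The outcome is undetermined, not reversed.
- **That several unadjusted comparisons inflate the overall false-positive rate.** No alpha and no significance-based success claim is stated, and a pilot built on estimates and intervals need not control family-wise error. The comparisons are also between randomized groups.
- **That the Table 1 rate targets are unlikely to be met jointly, or need a combining rule.** Such a calculation would have to cover every criterion at the actual arm sizes. Table 1 targets 40 chiropractors and Trial status reports 45 randomized, so figures for 15 per arm do not describe the trial. How the criteria combine is detail the full protocol may hold.

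**Conclusion.** The contradiction holds on the face of the document: three feasibility outcomes in the abstract and objectives, four in Measures, and no criterion for the fourth where one is said to be. The consequence is limited but real, because the feasibility conclusion is the pilot's main product and the document leaves open whether an effect estimate belongs in it.

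The figure of 0.10 to 0.19 supports one narrower statement: the chance probability in Statistical analysis should not be used to judge effectiveness potential. It rests on an assumed 5% reading, arms of 15 and 16 as in the example, and true response rates of 0.1 to 0.5. With the larger arms implied by the 45 randomized it would differ somewhat, but the control proportion would still be an estimate treated as known.

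**What to change.** Four wording changes, best made before outcome data are analysed:

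1. **Measures, opening paragraph.** Delete item (4), so that recruitment, adherence and retention are the key feasibility outcomes, as in the abstract and objectives.
2. **Same paragraph.** Refer Table 1 to items (1) to (3).
3. **Measures, last paragraph.** Reword the effect-size sentence to say that effect estimates inform the choice of primary outcome and the sample size of the main trial, and do not enter the feasibility verdict.
4. **Statistical analysis.** Label the knowledge and self-efficacy comparisons exploratory. Report between-group differences with 95% confidence intervals in place of the chance probability, and amend the potential-efficacy row of Table 4 to match. The abstract already plans estimates with intervals for the rates, pain and the Neck Disability Index, so this extends the same approach.

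No extra data, participants or visits are needed. The small cost is that a favourable efficacy signal can no longer be cited as evidence of feasibility.

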## Background

Translating evidence into clinical practice is challenging. As a result, patients often fail to receive optimal care and may be exposed to unnecessary harm [1]. The Medical Research Council (MRC) guidelines on complex intervention evaluation recommends conducting feasibility and/or pilot studies with an aim to improve the effectiveness and efficiency of interventions and to address the challenges in translating research into real-world settings [2, 3]. One example where these recommendations apply is within clinical sites that deliver interventions for individuals with musculoskeletal (MSK) conditions.

Neck pain results in an enormous social, psychological, economic burden to society and is a leading cause of physical disability [4]. The estimated annual incidence of neck pain ranges between 10.4 and 21.3 % with a higher incidence noted in office and computer workers [5]. In chiropractic practice, neck pain accounts for approximately 25 % of initial consultations [6]. Opinions vary widely on what causes neck pain and how best to manage it [7]. The vast majority of patients with neck pain have symptoms that are “non-specific” in nature that cannot be attributed to a specific disease process or anatomical structure [8]. Perhaps as a result, relatively few treatments have been shown to achieve meaningful and sustained improvements in pain, physical function, and disability, despite associated high costs of neck pain [9].

Current evidence suggests a multimodal approach including manual therapy, providing self-management support to patients, and physical activity including exercise as an effective treatment strategy for acute and chronic neck pain [10]. The promotion of physical activity, including exercise, is a first-line treatment considered important in the prevention and treatment of musculoskeletal pain and its related co-morbidities [11]. For a minority of patients, clinician-delivered interventions and pharmacological treatments are appropriate, and in fewer cases, multidisciplinary pain management and/or surgery may be indicated [12]. In addition, multi- and/or inter-disciplinary multimodal therapy, as well as cross-sectorial integrated medical care appear to be cost-effective strategies for managing chronic pain [13].

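### The patient-recruitment criterion (five in 6 weeks) needs about twice the rate the protocol plans for (five in 3 months), and nothing reconciles the two

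*Protocol article*

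**What the plan says.** Patient recruitment is one of the primary feasibility outcomes named in the Abstract. Two places in the protocol article attach a pace to it.

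- Measures, Table 1 (criteria to assess feasibility, patient recruitment): "Trial acceptance rate: 5 patients within 6 weeks of recruitment notice". The row beneath gives a target of 150 patients.
- Recruitment of patients: "The expected recruitment of 5 patients within 3 months is reasonable assuming an average practice volume of 85 patient visits per week per chiropractor". The section opens with "Participating chiropractors will each recruit up to five consecutive new patients with neck pain". It puts the neck-pain share of those weekly visits at one quarter.

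That 25% carries a citation. The Background uses the same citation for a different base: "neck pain accounts for approximately 25 % of initial consultations".

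The patient criteria limit enrolment to neck pain presenting as a new condition, and exclude anyone who had chiropractic care for neck pain in the preceding 3 months. On language, chiropractors qualify if "Fluent in spoken English or French", while patients must be "Able to understand and speak English to complete all study questionnaires".

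Under Trial status, 45 chiropractors have been randomized and patient recruitment has begun.

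**The concern.** The number of patients is the same in both places, but the window in the criterion is less than half the window in the plan. No section explains why. If the plan is right about pace, the criterion will tend to report a shortfall even when recruitment goes as expected. If the criterion is right, the planning sentence understates the pace the trial needs.

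The result is used. The primary objective is to show whether a full trial is feasible, and Study limitations says that meeting this objective is necessary for future funding applications. With two windows in print and no statement of which one decides, the choice could be made after the counts are known.

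The volume argument might have settled the matter by showing that 6 weeks is comfortable. It cannot, because its 25% is attached to visits in one section and to initial consultations in another, and only new patients can enrol.

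**Working it through.** **Inputs.** Five patients in 6 weeks (Table 1). Five per chiropractor in 3 months, 85 visits per week and 25% neck pain (Recruitment of patients). Thirty chiropractors and 150 patients (Abstract). Three months is taken as 13 weeks, with 12 as the alternative.

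**The plan's own total.** 30 × 5 = 150, as stated. The 3-month figure is a judgement of what is reasonable, not the result of a formula, so it cannot be reproduced in the same way.

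**Required against planned rate.**
- Required: 5/6 = 0.83 patients per week.
- Planned: 5/13 = 0.38 per week (5/12 = 0.42).
- Ratio: 13/6 = 2.17 (12/6 = 2.0).

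**Expected count at 6 weeks at the planned rate.**
- Per chiropractor: 5 × 6/13 = 2.3 (5 × 6/12 = 2.5).
- Thirty chiropractors: 30 × 2.31 = 69 (30 × 2.5 = 75), against 150.
- The 45 already randomized: 45 × 2.31 = 104 (45 × 2.5 = 112.5), still below 150.

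Table 1 does not say whether the row is judged per chiropractor or overall. The plan falls short on either reading.

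**Chance that one chiropractor has at least five by 6 weeks.** The document gives no arrival model, so each line below rests on an assumption.

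| Reading of five within 3 months | P(at least 5 by 6 weeks) |
|---|---|
| Poisson, mean 5 per 13 weeks | 8.5% |
| Poisson, mean 5 per 12 weeks | 10.9% |
| Same means with between-practice variation (negative binomial, shape 1 to 4) | 12% to 19% |
| Exactly five, spread uniformly over 13 weeks: (6/13)^5 | 2.1% |
| Rate that reaches five in 13 weeks with probability 80% | 20% |
| The same with probability 90% | 31% |
| The same with probability 95% | 41% |

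For the first line, the mean is 2.308, so P = 1 − e^(−2.308) × (1 + 2.308 + 2.663 + 2.048 + 1.182) = 1 − 0.915 = 0.085. Under Poisson, an even chance of passing at 6 weeks needs about 10.1 patients per 13 weeks, about twice the plan.

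The Poisson model with mean 5 also gives only a 56% chance of five or more at 3 months. It is a scale for the mismatch, not a forecast.

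**Volume figure.** 85 × 0.25 = 21.25 neck-pain visits per week: 127.5 in 6 weeks and 276 in 13. Five patients would be 3.9% or 1.8% of these, so as written the figure rules out neither window. But it counts visits. The number wanted is new neck-pain consultations × share eligible × share consenting, and the document gives none of these.

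As an illustration only, assume that 3% to 10% of visits are new patients and that 20% to 50% of new neck-pain patients are eligible and consent.
- Low: 85 × 0.03 × 0.25 × 0.20 = 0.13 per week, or 0.8 in 6 weeks and 1.7 in 13.
- High: 85 × 0.10 × 0.25 × 0.50 = 1.06 per week, or 6.4 in 6 weeks and 13.8 in 13.

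Five lies inside both ranges, so volume does not decide between the windows.

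**The case against.** The best defence is that Table 1 holds the only criterion. The 3-month figure is a planning statement, and with its cap of five it may mark an outer limit rather than an average pace. A benchmark tighter than the time allowed can coexist with it. No stop/go rule is attached to the row, the main analysis is descriptive, and Table 2 measures recruitment by eligibility and participation proportions. All of this stands. It lowers the stakes, but the document never says that the tighter benchmark is deliberate or why the faster pace should be expected.

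Some stronger readings are tempting but not supported:

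- That identical data would pass one criterion and fail another. There is one criterion and one planning sentence.
- That about 91% of on-plan chiropractors will fail. This treats five in 3 months as a constant Poisson mean; other readings leave up to 41% passing. Strong front-loading after the notice would also raise the pass rate, though the document describes none.
- That 6 weeks is unattainable. The volume figures do not show it.
- That the cited source is misused. The source is not available here; only the change of base between the two sections can be shown.
- That practices with French-fluent chiropractors cannot reach five. The language criteria do differ, but nothing gives the number of French-only practices or their share of English-speaking patients.

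**Conclusion.** The inconsistency is real and lies in current text. The criterion demands about 2.0 to 2.2 times the planned pace. At the planned pace, 2.3 to 2.5 patients per chiropractor are expected at 6 weeks, about 69 to 75 of 150 overall. The chance of reaching five is about 8% to 11% under a constant Poisson rate and about 2% to 41% across the other readings tried. A practice recruiting as planned would usually miss the criterion under every one of them.

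The ratio and the expected counts need only a roughly even pace and a 12- or 13-week reading of 3 months. The probabilities depend on the assumed arrival pattern and should be quoted as a range. The volume sentence supports neither window, because its base is all visits while enrolment is confined to new patients. The document does not show which window was intended.

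**What to change.** Reconcile the two sections before outcome data are analysed:

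1. Name one deciding window and state whether it is judged per chiropractor or overall. If 6 weeks is kept, justify the faster pace. If 3 months is chosen, give the reason and date the change, since recruitment has begun and a threshold should not be relaxed silently.
2. Report the 6-week and 3-month counts, each with a 95% confidence interval, whichever window decides.
3. Restate the expected yield as new neck-pain consultations per week × share eligible × share consenting, in place of 85 visits × 25%.

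The cost is one table row and one planning sentence. Chiropractor eligibility should stay as it is: 45 are already randomized, and restricting it now would mean exclusions after randomization. The English/French difference can at most be described, for example by reporting patient recruitment by practice language.
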